### Providers

We are performing a two-group RCT, testing the effectiveness of translating the COPD guidelines into clinical practice, with primary care physicians’ practices as the unit of randomization and evaluation. The intervention arm receives an intervention of academic detailing, an iPad-based patient activation tool that will be placed in the examination rooms, a netbook running a COPD guideline decision support tool, a COPD patient education toolkit including a website, and a portable spirometer and a printer. The usual care arm receives visits on the same schedule as the academic detailing visits, a website link to the GOLD Guidelines, a printer, and a portable spirometer. The intervention is of one-year duration. We are evaluating the use of the interactive tool and use of the patient activation tool through tracking software.

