### Measures

Data collection for practices includes: type of practice (HMO, single specialty, etc.); degree of managed care; service options (dietitian, nurse counseling, etc.,); numbers of personnel (physicians, RN, LPN, Nurse Practitioners, medical assistants, physician assistants, clerical, other); use of non-physician personnel, use of ancillary services in office (office laboratory, phlebotomy, dietitian, consultants); ancillary services in the building; who returns phone calls (physician vs. other); record systems (computerized, written, dictated); physical environment (rural, urban, suburban), socioeconomic class of patients seen; office organization (evening hours, weekend hours); and volume of visits (number scheduled, number of unscheduled, total number of patients, number of patient care hours, number no shows). Data collection of providers includes: 1) demographic information (age, gender), years in practice, type of provider (physician, nurse practitioner, physician assistant), specialty (general practitioner, family physician, obstetrics/gynecology, medicine/pediatrics, general internist, other); 2) practice characteristics (number of office visits, nursing home visits, and home visits seen in a typical week); 3) self-report of preventive screening (cholesterol screening, glucose screening for diabetes, self-report of counseling for smoking cessation, diet, physical activity) and 4) self-reported familiarity with COPD guidelines and feelings about COPD guidelines. Patient information from medical records includes: 1) socio-demographic factors- age, gender, race/ethnicity, insurance status, pharmacy benefits, marital status, number of visits in past year; 2) COPD risk factors (tobacco smoke, occupational dusts and chemicals, smoke from home cooking and heating fuel); 3) co-morbid conditions (i.e., coronary heart disease, congestive heart failure, arrhythmias, hypertension, stroke, liver disease, renal disease, arthritis, diabetes, malignancies, Parkinson’s disease, depression, osteoporosis); 4) functional status; 5) cachexia; 6) medications; 7) vital signs-height, weight, waist circumference, body mass index; 8) laboratory- hemoglobin, hematocrit; 9) provider documentation of weight loss, dietary assessment, dietary treatment or referral, physical activity assessment, and treatment for smoking cessation advice/ counseling/referral; 10) indicators needed to perform spirometry: dyspnea (worse with exercise, persistent, increased effort to breathe), chronic cough, chronic sputum 11) provider documentation of the need for pharmacotherapy; 12) provider documentation of adverse effects of COPD medications; and 13) intervention specific outcomes- documentation of *MyLungAge* in the chart, using printed SOAP notes or patient education page notes, use of the study smoking cessation material, and documentation of referral to the *MyLungAge* website. Data collection by chart audit is performed at baseline and again one-year post intervention. In addition, charts are audited for family history of COPD, smoking status, chest x-rays, ECGs, α_1_-antitrypsin deficiency screening, COPD symptoms (prolonged or progressive cough, sputum production, persistent or progressive dyspnea), exposure to lung irritants, exposure to secondhand smoke, documentation of spiromety, documentation of pulmonary disease, COPD, cystic fibrosis, interstitial lung disease, sarcoidosis, tuberculosis, pulmonary hypertension, thoracic surgery, immunizations and vaccines. Adherence to the COPD guidelines is based on an adherence tool developed by a consensus panel of 6 individuals with expertise in COPD and will include information on documentation of: exposure to tobacco smoke and occupational dust and chemicals; smoking status; appropriate treatment, increase in symptoms, influenza and pneumococcal vaccine; need for oxygen therapy; and assessment of history of CVD or CVD risk factors.

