
### Sample size considerations

The primary aim of this RCT is to determine and compare the proportion of participants who are appropriately diagnosed with COPD between the intervention and usual care arm. The clusters (i.e. practices) are randomly assigned to the intervention or usual care arm. Taking the intra-cluster correlation into account in the planning phase of the study is critical since failure to do so may result in an underpowered study. The intra-cluster correlation (r) is estimated to be between 0.01-0.02 based on previous findings [22]. For this study, we enrolled 30 practices, 15 for each group. Using a two-side type I error of 5%, the projected number of random charts per practice needed for a power of 80% is 35 for r=0.01 and 52 for r=0.02. Similarly, we assume the estimated percentage of patients who were diagnosed with COPD varied from 6% for the control group and 12% for the intervention group. The selection of 100 charts per practice in the random retrospective chart audits gives us reasonable power for all projected COPD outcomes. A total of 3000 charts for the study provide greater power for multivariate analyses, detecting interaction effects, robustness to violations of model assumptions. Given that we have audited 3,604 baseline charts, we have increased efficiency to detect weaker relationships between variables.

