### Statistical analyses

Initially, descriptive statistics such as frequency tables for each categorical variable, and minimum, maximum, range, median, mean and standard deviation for each continuous variable will be used to summarize the data as well as detect outliers, data entry mistakes, and missing values. Classical longitudinal plots will be used to identify trends over time in both practice and individual levels. Chi-squared tests, t-tests or non-parametric tests will be used to assess the effectiveness of the randomization procedures by comparing intervention and control groups on baseline variables. Data analyses will be performed using SAS 9.1.3 (SAS Institute, Inc, Cary, North Carolina).

Following intention-to-treat principles, all participants who have been randomized to the two conditions will be included in the analyses. We hypothesize that a greater proportion of patients in the intervention arm will be appropriately diagnosed with COPD after one year compared to the usual care arm. We will use both generalized linear models using GEE (generalized estimating equations) approach and generalized linear mixed models to evaluate the independent effect of intervention after adjusting for patient and provider level covariates, important demographic and confounding factors. To compare COPD guideline adherence to the treatment algorithm recommended for primary care physicians after a one-year intervention in the usual care arm compared to the intervention arm, we will examine the dichotomous variable of whether or not a provider will adhere to the COPD treatment algorithm after a one-year intervention.

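### Guideline adherence is reduced to one yes/no per provider, and the power statement for all COPD outcomes rests only on the diagnosis calculation and does not support adherence

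*Protocol article*

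**What the plan says.** **Measurement.** Under Measures, the article says "Adherence to the COPD guidelines is based on an adherence tool developed by a consensus panel of 6 individuals". The tool covers several documented items: exposures, smoking status, treatment, worsening symptoms, two vaccines, need for oxygen, and cardiovascular history or risk.

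**Analysis.** Under Statistical analyses, the adherence comparison is fixed in one sentence: "we will examine the dichotomous variable of whether or not a provider will adhere to the COPD treatment algorithm after a one-year intervention".

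**Power.** Under Sample size considerations, the primary aim is to "compare the proportion of participants who are appropriately diagnosed with COPD between the intervention and usual care arm". With 15 practices per arm, 6% against 12%, and a two-sided 5% test, "the projected number of random charts per practice needed for a power of 80% is 35 for r=0.01 and 52 for r=0.02". The text then extends this: "The selection of 100 charts per practice in the random retrospective chart audits gives us reasonable power for all projected COPD outcomes". It gives no expected adherence rate, no number of providers and no denominator for adherence.

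**Charts.** Methods/Design describes two audits: an identified, consented sample of at-risk or COPD patients, used to look at management before and after the intervention, and a de-identified random audit. Outcomes gives 125 randomly selected patients and 180 charts in total per practice. The size of the at-risk or COPD sample is not given separately.

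**The concern.** There are two linked problems.

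1. **The outcome.** Several items, on several patients per provider, become one adherent or not-adherent label. A provider who moves from meeting few items to meeting most of them counts as no change if both scores fall on the same side of the cut. Gains are seen only where they cross it, so the answer depends on where the cut lies.

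2. **The power statement.** A calculation for diagnosis uses every audited chart in the denominator. Adherence to a COPD treatment algorithm, if judged in patients with COPD, uses only a small part of them. That part also depends on the diagnosis rate, which the intervention is meant to raise, so the arms would be compared on patient groups that the intervention itself helped to form.

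At stake is the guideline-implementation comparison. A real improvement could be missed, and a null result could be read as evidence of no effect because the article says power was reasonable for all COPD outcomes.

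**Working it through.** **Step 1. Reproduce the plan's own figure.** Inputs from Sample size considerations: 6% v 12%, 15 practices per arm, two-sided 5%, 80% power, r = 0.01 or 0.02.

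- Two-proportion sample size with continuity correction: n = 389 per arm (356 without).
- With design effect 1 + (m − 1)r, charts per practice are m = n(1 − r)/(15 − n·r).
- r = 0.01: 389 × 0.99/(15 − 3.89) = 385.11/11.11 = 34.7, so 35.
- r = 0.02: 389 × 0.98/(15 − 7.78) = 381.22/7.22 = 52.8, against the stated 52.

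The figures reproduce to within rounding. For diagnosis, 100 charts per practice give about 98% (r = 0.01) or 92% (r = 0.02) power. The calculation is sound for diagnosis and contains nothing about adherence.

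**Step 2. COPD charts in the random audit.** 100 × 0.06 = 6 and 100 × 0.12 = 12 per practice, or 15 × 6 = 90 and 15 × 12 = 180 per arm.

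**Step 3. Detectable difference for a patient-level yes/no near 50% adherence** (the 50% is an assumption and gives the largest variance).

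SE = √(0.25·DE₁/90 + 0.25·DE₂/180), with DE₁ = 1 + 5r and DE₂ = 1 + 11r. Detectable difference = (1.96 + 0.84) × SE.

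| r | DE₁ | DE₂ | SE | Detectable difference |
|---|---|---|---|---|
| 0.01 | 1.05 | 1.11 | 0.0668 | 18.7 points |
| 0.02 | 1.10 | 1.22 | 0.0689 | 19.3 points |
| 0.05 (assumed) | 1.25 | 1.55 | 0.0750 | 21.0 points |

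With the 125 charts named under Outcomes (7.5 and 15 COPD charts per practice), the difference is 16.9 to 17.6 points for r = 0.01 to 0.02. In terms of power with 100 charts and r = 0.01 to 0.02: 31–33% for 50% v 60%, 60–63% for 50% v 65%, and 85–87% for 50% v 70%.

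**Step 4. The outcome as worded, one yes/no per provider.** The number of providers is not stated, so K = 1 to 5 per practice is assumed, with provider-level r from 0 to 0.1. Effective n per arm = 15K/(1 + (K − 1)r). Power = Φ{[d√n − 1.96√(2p̄(1 − p̄))]/√(p₁q₁ + p₂q₂)}, with p₁ = 0.5, p₂ = 0.7, d = 0.2 and p̄ = 0.6.

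| Providers per practice | Power, 50% v 70% |
|---|---|
| 1 | 20% |
| 2 | 32–35% |
| 3 | 42–49% |
| 4 | 50–61% |
| 5 | 56–71% |

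Without any clustering, 93 providers per arm would be needed for 80% power; 93/15 = 6.2, so at least 7 per practice. Auditing more charts does not raise the number of providers.

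**Step 5. Charts behind each provider's label.** If 3 providers (assumed) share 100 charts, each has about 33. The binomial chance of 2 or fewer COPD charts is 68% at a 6% rate and 22% at 12%. Many labels would rest on very few patients, and on fewer in the usual care arm.

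**Step 6. The counter-case.** Suppose that the charts beyond the 125 random ones, 180 − 125 = 55 per practice, were all at-risk or COPD patients (an assumption) and were analysed per patient. Effective n per arm = 15 × 55/(1 + 54r) = 536 (r = 0.01) or 397 (r = 0.02). Power for 50% v 60% is then 91% or 81%.

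**The case against.** The strongest reply is that 6 and 12 charts are not the right denominator. Methods/Design assigns management to the identified at-risk or COPD sample, and several tool items (smoking status, exposures, vaccines, cardiovascular risk) can be scored in patients at risk but without COPD. Step 6 shows that a patient-level analysis of such a sample could be well powered. This stands as a limit on the size of the problem. It does not support the power statement, which refers to the random audit, and it does not help a provider-level yes/no. The sample's yield of COPD patients is also unclear, since under Patients the invitations went to a random selection of active patients aged 40 or older.

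Three stronger readings are tempting, and the document does not support them.

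- A reader might infer that a provider-level outcome contradicts "practices as the unit of randomization and evaluation". It does not: Methods/Design lists outcomes at practice, provider and patient level.
- A reader might infer that clustering is ignored for adherence, or that the cut is arbitrary. The sentence on GEE and mixed models directly precedes the adherence sentence and is not confined to diagnosis. The cut and the scoring may be in an analysis plan that is not shown. What is fixed here is the decision to dichotomise per provider.
- A reader might infer a known, large power loss from dichotomising. Its size turns on the cut, the number of providers and the variation between patients, none of which is stated. With some cuts the loss could be small.

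**Conclusion.** The concern holds in a limited form. The adherence outcome is fixed as one yes/no per provider although the tool yields graded, patient-level data, so information is lost and the result depends on the cut. The statement of reasonable power for all projected COPD outcomes is unsupported for adherence.

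It should not be called false. Even on 6 and 12 charts, a patient-level yes/no has about 85% power for a 20-point difference, and the at-risk or COPD sample may add charts.

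The 19-point figure assumes adherence near 50%, r of 0.01 to 0.02, and COPD charts from the random audit only; it applies to a patient-level yes/no and to no other outcome. The provider-level result, below 80% power for 50% v 70%, assumes 1 to 5 providers per practice. Adherence is not the primary aim, and the diagnosis calculation is unaffected.

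**What to change.** 1. Make the adherence analysis the patient-level proportion of applicable tool items met, using the GEE or mixed model already planned, with practice as the cluster and providers nested within it.
2. Use the identified at-risk or COPD cohort as fixed at the baseline audit, so that the denominator does not depend on diagnoses that the intervention changes. State its size.
3. Keep the provider yes/no as a descriptive summary.
4. Limit the power statement to COPD diagnosis, or add a detectable difference for adherence computed for the outcome and cohort actually used. The 19 points should not be carried over to the item score or to the baseline cohort.

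The cost is a changed adherence summary and a less favourable power statement. No new data are needed, since the tool items and both audits are already planned.

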### Outcomes

Outcomes are being measured by medical record audit of 125 randomly selected patients per practice at baseline and one year post intervention; a random chart audit of de-identified patient outcomes both pre- and post-intervention to determine the degree of selection bias inherent in the informed consent process; and a chart audit of those patients who gave informed consent on the iPad patient activation tool in the intervention practices. A total of 180 charts are being audited per practice.

#### Time plan

The development of the program began in July, 2009 and the study will be completed in June, 2014. Provider recruitment started in October, 2010 and was completed in March, 2012 and patient recruitment began in December, 2010 and was completed in June, 2012.

## Discussion

In order to effectively overcome COPD guideline implementation problems, we need to better understand why primary care providers are underdiagnosing and undertreating patients with COPD and the barriers and facilitators to more fully implement the COPD guidelines. This study has allowed us to incorporate the insights discovered through qualitative methods in Phase I into the development of the provider interactive decision support tool on the netbook combined with the academic detailing materials. In addition to better understanding provider barriers and facilitators to guideline implementation, understanding patient knowledge, attitudes and behavioral intentions regarding COPD diagnosis and management is crucial. This information has helped us in developing appropriate patient activation tools, patient education and self-management tools, and the patient/provider shared decision-making screen incorporated into the *MyLungAge* iPad tool. We are in the process of utilizing these tools developed in Phase I, in the cluster design clinical trial in Phase II to determine the effectiveness of these tools in improving COPD guideline implementation. The results of this RCT will provide us with valuable insight into how to enhance implementation of COPD guidelines in primary care practices.

## Abbreviations

COPD: Chronic Obstructive Pulmonary Disease; RCT: Randomized clinical trial; GOLD: Global Strategy for the Diagnosis, Management, and Prevention of Chronic Obstructive Lung Disease; ECG: Electrocardiogram; CVD: Cardiovascular disease; GEE: Generalized estimating equation.
